## **Description of the methods for evaluating the response**

### Laboratory determinations

Blood workup: red cells, hemoglobin, hematocrit, mean corpuscular volume, mean corpuscular hemoglobin, mean corpuscular hemoglobin concentration, platelets, leukocytes, and leukocyte formula.

Biochemistry: aspartate aminotransferase, alanine aminotransferase, LDH, alkaline phosphatase, GGT, total bilirubin, uric acid, creatinine, urea, calcium, phosphorus, glycemia, cholesterol, triglycerides, and albumin.

Pregnancy test.

CD4+ T lymphocyte count.

Determination of HIV viral load using ultrasensitive methods.

Evaluation of viral tropism, by phenotyping.

Measurement of latent reservoir of HIV-1 (see Annex IV)

Direct measurement of residual viremia using the real time PCR (SCA) and Episomal DNA circles with 2-LTRs (see Annex IV)

Immune Activation Markers as indirect measurement of residual viremia (see Annex IV)

# These analyses will be carried out in the laboratories of Hospital Ramón y Cajal as part of the routine monitoring of antiretroviral therapy in HIV-infected patients. The only exceptions to this are the evaluation of viral tropism (Monogram, California USA) and measurement of the latent HIV reservoir, which will be carried out in an external laboratory (Molecular Immunobiology Laboratory, Hospital General Universitario Gregorio Marañón (Dra [name]). The methods used to carry out these determinations are specified in Annex IV.

# ADVERSE EVENTS

## **Minimum required information**

The research team will follow up any adverse events that occur during the study. They will record the time of onset, the duration, intensity, course, and outcome of the event in order to evaluate the relationship of causality between the adverse event and the medication.

Recording of adverse events will be by a generic question of the following type: Have you noticed anything since you started taking the medication? or after spontaneous notification by the patient.

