## **Analysis and withdrawal criteria**

The patient can decide to withdraw from the study at any time. The investigator can also decide to withdraw a patient if the patient does not fulfill the norms of the protocol. Virological failure or development of toxicity to any of the study drugs will also be a reason for leaving the study.

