**STUDY PLAN**

| ***Day*** | ***Baseline***  ***1*** | ***Baseline 2*** | ***Month 3*** | ***Month 6*** | ***Month 9*** | ***Month 12*** | ***Month 15*** | ***Month 18*** |
| --- | --- | --- | --- | --- | --- | --- | --- | --- |
| **Informed consent** | X |  |  |  |  |  |  |  |
| **Clinical history** | X | X | X | X | X | X | X | X |
| **Physical examination1** | X | X | X | X | X | X | X | X |
| **Pregnancy test (women)** |  | X |  |  |  |  |  |  |
| **Determination of viral tropism** | X |  |  |  |  |  |  |  |
| **Inclusion criteria** | X |  |  |  |  |  |  |  |
| **Laboratory determinations2** | X | X | X | X | X | X | X | X |
| **Administration of drugs** |  | X | X | X | X | X |  |  |
| **Evaluation of adverse effects** |  | X | X | X | X | X |  |  |

1 Includes heart rate and blood pressure.

2 Includes blood count, biochemistry, habitual immunological and virological monitoring, as well as measurement of the size of the latent reservoir, residual viremia and immune activation markers.

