## **Imputability criteria**

Adverse events will be graded by their relationship of causality with the drug according to the algorithm of Karch and Lasagna (1977) as:

- *Definite*: There is a plausible time sequence between administration of the drug and onset of the adverse event—this event follows a known response pattern to the suspected drug, improves when the drug is suspended, and reappears when it is re-administered.
- *Probable*: There is a plausible time sequence between administration of the drug and onset of the adverse event—this event follows a known response pattern to the suspected drug, and cannot be explained otherwise.
- *Possible*: There is a plausible time sequence between administration of the drug and onset of the adverse event—this event follows a known response pattern to the suspected drug, but it can be explained otherwise.
- *Conditional or improbable*: There is a plausible time sequence between administration of the drug and onset of the adverse event—this event does not coincide with the adverse events described for the drug and can be explained otherwise.
- *Not related*: There is no plausible time sequence between administration of the drug and onset of the adverse event—this event does not coincide with the adverse reactions described for the drug and it can be explained otherwise.

The adverse event will also be classified according to its intensity:

*Mild*: Does not cause limitations to usual activity. Does not require additional treatment.

*Moderate*: Causes some limitation to daily activities and may or may not require further treatment.

*Severe:* Leads to inability to carry out daily activities and requires further therapy.

In general, **severe and/or life-threatening adverse reactions** will be considered to be those that are possibly or probably related to the medication and that fulfill any of the following criteria:

- an event that leads to death of the volunteer or patient
- an event that threatens the life of the volunteer or patient
- an event that requires hospitalization or prolongs existing hospitalization
- an event that causes permanent or significant disability or invalidity
- an accidental or voluntary overdose
- an event that reveals a congenital anomaly or birth malformation and malignant processes
- an important medical event, understood as an event that requires urgent intensive treatment

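### Adverse events are recorded only by patient-reported routes, and the intensity scale cannot grade symptomless laboratory toxicity

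*Protocol*

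**What the plan says.** Section 8.1 opens with a general duty: "The research team will follow up any adverse events that occur during the study". It then says how events come to be recorded: "Recording of adverse events will be by a generic question of the following type: Have you noticed anything since you started taking the medication". The one alternative it gives is a report that the patient volunteers. No further route is named.

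Section 8.2 has one intensity scale with three levels:
- Mild sets two conditions, one on activity and one on treatment: "Does not cause limitations to usual activity. Does not require additional treatment".
- Moderate turns on a partial restriction of activity and leaves treatment open either way.
- Severe again joins two conditions, and both must be met: "Leads to inability to carry out daily activities and requires further therapy".

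Section 8.2 also has a separate list that defines severe or life-threatening reactions. It covers death, threat to life, hospitalization, disability and the need for urgent intensive treatment, among others. It applies to events possibly or probably related to the medication.

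The study plan in section 7.2 schedules laboratory determinations and physical examination with heart rate and blood pressure at every visit. The laboratory footnote reads "Includes blood count, biochemistry, habitual immunological and virological monitoring". Section 7.3.1 lists the analytes, among them transaminases, bilirubin and creatinine, and describes the testing as routine monitoring. Section 5.4 adds that "development of toxicity to any of the study drugs will also be a reason for leaving the study", without defining toxicity.

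**The concern.** An added drug can raise a liver enzyme or creatinine, or lower a blood count, in a patient who feels well. The protocol measures these values at every visit, but its recording rule draws only on what the patient notices. If an investigator records such a finding anyway, the intensity scale has no term for the size of a laboratory change.

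The trial is phase II, is filed as the first in a new indication, and adds a drug for 12 months in patients with long-suppressed virus. With 10 patients, one or two missed or undergraded events would change the safety picture. An event never opened as an adverse event also gets no onset, causality, course or outcome assessment. Later tabulation of laboratory values could not restore these.

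**Working it through.** The protocol gives no figure to reproduce. The check sets the sections side by side and counts.

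**1. Recording routes (8.1).** Generic question: depends on the patient noticing. Spontaneous notification: depends on the patient noticing. Routes that start from a laboratory, vital-sign or examination result: none stated.

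**2. What is measured (study plan, 7.3.1).**
- Laboratory determinations: 8 of 8 visits. Physical examination with heart rate and blood pressure: 8 of 8.
- Evaluation of adverse effects: 5 of 8 visits (Baseline 2 to Month 12), each of which also has laboratory tests.
- Items listed in 7.3.1: 15 biochemistry and 9 blood count, so 15 + 9 = 24 per panel.
- On-drug panels: Months 3, 6, 9 and 12 give 4 visits × 10 patients = 40. This assumes that all 10 patients attend every visit and that Baseline 2 blood is drawn before the first dose.

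The 40 counts panels with no written path into the adverse-event record. It does not estimate how many toxicities would be missed; the protocol gives no expected frequency.

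**3. What the intensity scale can grade (8.2).** Crossing three levels of activity limitation with treatment needed or not gives 3 × 2 = 6 combinations:

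| Activity | No treatment needed | Treatment needed |
| --- | --- | --- |
| No limitation | Mild | no grade |
| Some limitation | Moderate | Moderate |
| Inability | no grade | Severe |

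Four of the 6 combinations have a grade. A symptomless abnormality lies in the first row by definition. It is Mild if untreated, at any magnitude, and ungraded if treated. Moderate and Severe both require limitation of activity, so it cannot reach either.

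**4. What the seriousness list adds (8.2).** The list does not depend on daily activity. A silent abnormality that threatens life, leads to hospitalization or needs urgent intensive treatment qualifies, if someone recognises it and judges it possibly or probably related. A marked rise that meets no item on the list is left with the result of step 3.

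**5. Link to withdrawal (5.4).** Toxicity is a reason for leaving the study, but 5.4 refers to neither 8.1 nor 8.2, and neither of those defines toxicity. The sections do not contradict each other; they are unconnected.

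**The case against.** The strongest reply is that 8.1 need not be exhaustive. Its heading speaks of minimum information, it opens with a duty covering any event, and it never says that other sources are barred. The case report form, the Investigator Brochure and the service's operating procedures are not shown and may deal with laboratory findings. The reaction form in Appendix E asks for relevant laboratory results. Safety is not a listed objective, and the reservoir estimate is unaffected.

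Part of this stands. A reader might infer that laboratory toxicity goes unrecorded altogether. The protocol does not support that: the values are measured at every visit and may well be on the case report form. What is missing is a stated route into the adverse-event record. The duty to follow up applies to events already identified, and the only text on identification names patient report. The Appendix E form is for suspected severe and unexpected reactions already recognised, so it does not serve detection.

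A reader might also infer that dangerous silent toxicity is simply graded Mild, or that grading rests on daily activity alone. Neither is right. Need for treatment is a second criterion, so a treated symptomless abnormality has no grade rather than Mild, and the seriousness list operates apart from intensity.

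Lastly, a reader might infer that nothing would flag such a patient or lead to withdrawal. Investigators may see the results through routine monitoring, and 5.4 does not require toxicity to be recorded first under 8.1. The supportable statement is that no written rule connects them.

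**Conclusion.** The point holds in limited form. The stated routes for recording adverse events are patient-reported and omit findings collected at 8 of 8 visits. The intensity scale leaves 2 of 6 combinations ungraded and cannot place a symptomless abnormality above Mild. Followed as written, the rules would undercount and undergrade silent toxicity that falls short of the seriousness list.

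The number of events affected cannot be estimated from the protocol. The conclusion rests on reading 8.1 and 8.2 as the operative rules; instructions in the unseen case report form or operating procedures could narrow the gap in practice. This should be corrected because it concerns how events are captured and graded at the visit, which 8.1 and 8.2 have already fixed and which an analysis plan cannot repair afterwards.

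**What to change.** - **Section 8.1:** add clinically significant laboratory, vital-sign and examination findings, new or worse than the two baseline assessments, as a source of adverse events beside the two patient-reported routes.
- **Section 8.2:** grade laboratory abnormalities by a named published laboratory toxicity scale chosen by the sponsor. Keep the activity-and-treatment scale for symptomatic events, and assign a grade to its two open combinations: no limitation but treated, and inability but untreated.
- **Section 5.4:** reconcile the word toxicity with 8.1 and 8.2. Any withdrawal rule or threshold is for the sponsor to decide.

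The cost is protocol wording and a matching adverse-event page in the case report form. The tests and examinations are already scheduled, so no visit, sample or patient is added. The small downside is that more events will be recorded and assessed.

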## **Imputability criteria**

Adverse events will be graded by their relationship of causality with the drug according to the algorithm of Karch and Lasagna (1977) as:

- *Definite*: There is a plausible time sequence between administration of the drug and onset of the adverse event—this event follows a known response pattern to the suspected drug, improves when the drug is suspended, and reappears when it is re-administered.
- *Probable*: There is a plausible time sequence between administration of the drug and onset of the adverse event—this event follows a known response pattern to the suspected drug, and cannot be explained otherwise.
- *Possible*: There is a plausible time sequence between administration of the drug and onset of the adverse event—this event follows a known response pattern to the suspected drug, but it can be explained otherwise.
- *Conditional or improbable*: There is a plausible time sequence between administration of the drug and onset of the adverse event—this event does not coincide with the adverse events described for the drug and can be explained otherwise.
- *Not related*: There is no plausible time sequence between administration of the drug and onset of the adverse event—this event does not coincide with the adverse reactions described for the drug and it can be explained otherwise.

The adverse event will also be classified according to its intensity:

*Mild*: Does not cause limitations to usual activity. Does not require additional treatment.

*Moderate*: Causes some limitation to daily activities and may or may not require further treatment.

*Severe:* Leads to inability to carry out daily activities and requires further therapy.

In general, **severe and/or life-threatening adverse reactions** will be considered to be those that are possibly or probably related to the medication and that fulfill any of the following criteria:

- an event that leads to death of the volunteer or patient
- an event that threatens the life of the volunteer or patient
- an event that requires hospitalization or prolongs existing hospitalization
- an event that causes permanent or significant disability or invalidity
- an accidental or voluntary overdose
- an event that reveals a congenital anomaly or birth malformation and malignant processes
- an important medical event, understood as an event that requires urgent intensive treatment

An **unexpected adverse event** is considered to be any experience not described (in its nature, severity, or frequency) in the product manual.

## **Procedures for the notification of adverse events**

Any suspicion of a severe and unexpected adverse event possibly related to the drug (adverse reaction) will be reported immediately by telephone to the study monitor. Within 3 days of the telephone report, a written, detailed, and suitably evaluated account of the event will be sent to the sponsor in accordance with RD 223/2004 and following the model set out in Appendix D published by the AEMPS (Spanish Medication Agency) to this effect (Appendix E of the protocol).

The investigator will be responsible for reporting the event to the monitor, sponsor, proprietary laboratory, the IRB of the study center, and the health authorities.

Initial reports and follow-up reports will identify the study subjects using a specific code for each of them.

The investigator will keep a detailed register of all adverse events. This register will be presented to the proprietary laboratory and the AEMPS on request.

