## **Procedures for notification of severe and unexpected adverse events.**

The sponsor will notify the AEMPS of all suspected severe and unexpected adverse events associated with the study drugs in accordance with current legislation.

The maximum period for notification will be 15 days, except when the suspected severe and unexpected adverse event has lead to the death of the subject, or has placed the subject’s life in danger. In this case, the event will be reported within the 7 natural days after knowledge of the event. The information can be completed within the following 8 days.

Reports to the AEMPS will be by [contact] or mail to Area de ensayos clínicos de la Subdirección General de Medicamentos de Uso Humano, [name].

Reports to the CAM will be via the contact person in Dirección General de Farmacia y Productos Sanitarios de la Consejería de Sanidad y Consumo de la CAM, Area de Investigación clínica y EPAs, [name]. [contact] [contact] E-mail: [[contact]](mailto:[contact]).

Reports to the IRB of Hospital Ramón y Cajal: [contact], at [[contact]](mailto:[contact]), or directly to [name] IRB Secretary.

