# ETHICS

## **General and specific norms for investigators**

The investigators will adhere strictly to the stipulations of this protocol, and will complete all the case report forms, which they will duly send to the sponsor or collaborating entity chosen by the sponsor to analyze the data.

The trial will be carried out in accordance with the recommendations for clinical trials and drug evaluation in humans, which appear in the Declaration of Helsinki (Appendix A), reviewed in Tokyo, Venice, Hong-Kong, South Africa, and Edinburgh (2000) and in current Spanish legislation on clinical trials.

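### Section 8.3 puts the site's only timed safety report behind expectedness and causality filters, so a serious reaction fully described in the product manual has no timed route to the sponsor in the visible protocol

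*Protocol*

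**What the plan says.** Four parts of the Protocol's adverse-event section matter here.

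- **8.2, seriousness.** Severe or life-threatening reactions are "those that are possibly or probably related to the medication and that fulfill any of the following criteria". Seven criteria follow, the first being "an event that leads to death of the volunteer or patient".
- **8.2, expectedness.** An event is unexpected if it is "any experience not described (in its nature, severity, or frequency) in the product manual".
- **8.3, the site's duty.** The trigger is: "Any suspicion of a severe and unexpected adverse event possibly related to the drug (adverse reaction) will be reported immediately by telephone". The call goes to the study monitor. A written account is due at the sponsor within 3 days of the call, on the Appendix E form. The next paragraph makes the investigator responsible for passing the event to the monitor, sponsor, manufacturer, IRB and authorities, with no time limit. All adverse events go into a register, of which 8.3 says: "This register will be presented to the proprietary laboratory and the AEMPS on request".
- **8.4, the sponsor's duty.** "The sponsor will notify the AEMPS of all suspected severe and unexpected adverse events associated with the study drugs", with a limit of 15 days. For fatal or life-threatening cases the limit is "within the 7 natural days after knowledge of the event".

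**The concern.** Limiting a report to unexpected reactions suits the sponsor's onward report to the regulator, and 8.4 already contains that limit. Section 8.3 is headed as covering adverse events in general, yet it applies the same limit one step earlier, at the site's first report. The site then makes the expectedness and causality judgements, and the result decides whether the sponsor is told at once.

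Two things are at stake. First, a serious reaction that the site regards as known may reach the sponsor late. Second, the sponsor's own 7- or 15-day duty depends on whether the event was unexpected. If the site misjudges that, the sponsor may have no timely chance to correct it. The question is not academic: the Protocol calls this a first trial for a new indication, and maraviroc is added to a background regimen of at least three drugs.

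**Working it through.** The check is a reading of the triggers, and the Protocol states no figure to reproduce. I take *severe* in 8.3 to mean the list of criteria in 8.2. If it meant the intensity grade instead, the expectedness and causality filters would still apply.

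**Step 1: the site's clock.** The call requires severe AND unexpected AND possibly related. The 3-day written report is counted from the call, so without a call there is no written deadline.

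**Step 2: the seriousness list.** The criteria in 8.2 are death, threat to life, hospitalization, disability, overdose, congenital anomaly or malignancy, and important medical event. That makes 7, of which 0 mention expectedness. For a reaction the manual fully describes, meeting any of the 7 does not start the clock, because 8.3 separately demands unexpectedness.

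**Step 3: what each kind of event triggers.**

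| Serious event | Timed site report in 8.3 | Sponsor's timed report in 8.4 |
| --- | --- | --- |
| Suspected related, differs from the manual in nature, severity or frequency | Immediate call, written account within 3 days of it | 7 or 15 days |
| Suspected related, described in the manual in all three respects | None | None |
| Judged unrelated | None | None |

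**Step 4: does any other visible text supply a deadline?**

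- *Register (8.3):* shown on request to the manufacturer and the agency; no deadline.
- *Case report forms (9.1):* investigators "will complete all the case report forms, which they will duly send to the sponsor"; no deadline.
- *Good Clinical Practice and the service's operating procedures (10.1):* invoked, but their content is not shown.
- *Filing list (10.3):* includes severe-event reports; no deadline.
- *Declaration of Helsinki (Appendix A):* a duty to inform the ethics committee of serious events; no deadline.
- *Appendix E, general instruction 2:* gives 7 days for fatal or life-threatening reactions without the word unexpected. Instruction 1 restricts the form to severe and unexpected reactions. The sentence after the 7-day rule gives 15 days to all *other* severe and unexpected events, so the 7-day group is a subset of the unexpected ones.

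**Step 5: the causality condition.** In 8.2 the grades definite, probable and possible each require the event to follow a known response pattern to the drug. The two lower grades are for events that do not match those described for it. An event unexpected in nature therefore tends to fail *possibly related*, while a fully described event fails *unexpected*. Read literally, the 8.3 trigger mainly catches known reactions of unusual severity or frequency.

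**Step 6: exposure.** 10 patients × 12 months = 120 patient-months if all complete. The Protocol gives no event rate, so no expected number of affected events follows.

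**The case against.** **Deaths.** A reader might infer that any death from a listed reaction escapes prompt reporting. The documents do not support that. The test in 8.2 has three parts, so a fatal case of a reaction listed only in milder form is unexpected and starts the clock. One death among 10 patients is already 10%, so frequency alone might make it unexpected, although 8.2 does not say how frequency is compared. The trigger is also any suspicion, a low bar. The manual is not shown, so whether it describes any reaction at fatal severity is unknown. This objection stands, and the point is limited accordingly.

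**Appendix E.** The 7-day sentence, read alone, seems to cover every fatal or life-threatening reaction. Its neighbouring sentences confine it, as shown above, so it does not close the gap.

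**Unseen rules.** Section 8.3 cites Royal Decree 223/2004 for the written report, 9.1 invokes current Spanish law, and 10.1 invokes Good Clinical Practice and local procedures. The case report form (Annex I) is not shown either. Any of these could carry a wider timed duty. A reader might infer that the sponsor *cannot* review the site's judgement in time; the documents support only that it *may* not be able to.

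**Omission rather than error.** Section 8.3 nowhere says that expected serious reactions need not be reported, and no two sections contradict each other. A reader might infer an exemption, but general recording and reporting duties remain. What survives is narrower: 8.3 states a rule for the site's first report and places the filter in it. That is a badly placed condition, not merely missing detail.

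**Size.** The count of 0 in 7 describes the structure of the rule. It is not a rate of missed events.

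**Conclusion.** The point holds in limited form. In the visible Protocol, a serious reaction that the manual describes in nature, severity and frequency has no timed report from site to sponsor. That includes a fatal reaction only where the manual describes it at that severity. Serious events judged unrelated also lack a timed report, and the causality grades make it harder for an event new in nature to qualify.

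The practical size is unknown and probably small in absolute terms, given one site and at most 120 planned patient-months on maraviroc. The conclusion rests on reading *severe* as the 8.2 list, on reading Appendix E as a whole, and on the visible text alone. It would lose most of its force if the cited law or the local procedures already require prompt reporting of all serious events. Even then, 8.3 should say so, because 9.1 tells investigators to follow this Protocol strictly. This is a patient-safety improvement worth making because it is cheap; it does not touch the efficacy analysis.

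**What to change.** Reword the opening of 8.3 so that the existing telephone call and 3-day written report apply to any adverse event meeting one of the seriousness criteria in 8.2, whatever its expectedness or causality grade. Add that, for this purpose, the 8.2 list applies without its relatedness condition. The site still records its expectedness and causality judgements, and the sponsor reviews both.

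Keep the unexpectedness and relatedness filters for the reports to the AEMPS and other health authorities (8.4, and the corresponding duty in 8.3) and for the Appendix E form. Because the current 3-day account is tied to that form, name a plain written report for the other serious events.

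The cost is a few additional calls and short reports from one site with 10 patients, plus small consistency edits across 8.2 to 8.4. Visits, samples and analyses are unchanged.
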